### 4.1. Sample Size

The sample size was estimated using a diagnostic accuracy study sample size calculator based on the methodology described by Akoglu et al. [19]. The calculation was based on an expected sensitivity of 95%, an expected specificity of 95%, a disease prevalence of 11%, a two-sided type I error rate of 5% (corresponding to a 95% confidence interval), and a margin of error of 10%. Based on these assumptions, a minimum of 167 patients was required. With an expected disease prevalence of 11%, this corresponds to approx. 18–19 patients with residual disease or recurrence and 148–149 patients without disease. To account for potential dropout, loss to follow-up, and non-evaluable samples, the target sample size was increased to 200 patients.

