### 3.4. Outcomes

The primary endpoint is to evaluate the sensitivity and specificity of ctHPV-DNA for the detection of recurrence in patients with HPV+ OPSCC, using clinically or radiologically verified recurrence as the reference standard. Time frame: A minimum of two years and up to three years after completion of primary treatment. Sensitivity will be calculated among patients who develop recurrence, whereas specificity will be calculated among patients who remain recurrence-free.

Secondary endpoints are defined as follows:Time to recurrence detected by ctHPV-DNA.Time to recurrence detected by clinical and/or radiological examination.Number of referrals to Cancer Fast-Track examinations based on a positive ctHPV-DNA test result without evidence of recurrence.Number of PET/CT scans performed because of a positive ctHPV-DNA test result without evidence of recurrence.

Quality of life (QoL), assessed using the Danish version of the Fear of Cancer Recurrence Questionnaire (short form), will be completed by patients after receiving the result of each blood sample.

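### The 10% margin of error stated for sensitivity is not what 18–19 cases give: the lower 95% limit lies about 19–22 points below the estimate, and the target condition is worded differently in the sizing and the endpoint

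*Protocol article*

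**What the plan says.** Section 4.1 (Sample Size) assumes sensitivity and specificity of 95% each, a prevalence of 11% and 95% confidence, and then states "a margin of error of 10%. Based on these assumptions, a minimum of 167 patients was required". It translates this into 18–19 "patients with residual disease or recurrence" and 148–149 patients without disease. The target is raised to 200 to cover dropout, loss to follow-up and samples that cannot be evaluated.

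Section 3.4 (Outcomes) defines the primary endpoint: "Sensitivity will be calculated among patients who develop recurrence, whereas specificity will be calculated among patients who remain recurrence-free". Section 6.3 (Statistical Methods) repeats these denominators, accepts as recurrence only what clinical or radiological examination confirms, and promises 95% confidence intervals without naming a method. Neither section mentions residual disease.

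**The concern.** Sensitivity is half of the primary endpoint and is the half that determines the sample size. A reader of Section 4.1 will expect a result at the planned 95% to come with a lower limit near 85% (95 − 10). Section 10 builds on an assumed high sensitivity when it suggests that testing could reassure patients and serve clinicians as a dependable tool. If the lower limit is really in the mid-70s, the planned result would not exclude a test that misses about one recurrence in four.

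The second question is who counts as a case. The sizing counts residual disease together with recurrence, while the endpoint speaks of recurrence alone. The first post-treatment sample is taken two months after treatment, when a positive result may reflect disease that never cleared. As worded, it is not settled whether such a patient is a true positive, a false positive or in neither denominator. With about 19 cases, each patient moves sensitivity by about 5 points (1/19 = 5.3%).

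**Working it through.** **Inputs, all from Section 4.1:** sensitivity 0.95, specificity 0.95, prevalence 0.11, two-sided 5% (z = 1.96), margin 0.10, stated minimum 167, target 200.

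**1. Reproducing the plan's figure.** Wald precision formula:

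- cases = z² × p(1 − p) / d² = 3.8415 × 0.95 × 0.05 / 0.01 = 18.25
- total = 18.25 / 0.11 = 165.9, that is 166, one short of the stated 167 and within rounding
- 167 × 0.11 = 18.4 cases, which is the 18–19 in the text
- specificity alone: 18.25 / 0.89 = 20.5 patients in total, so sensitivity drives the size

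**2. Where the 10 points come from.** The Wald half-width is 1.96 × √(0.95 × 0.05 / n):

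- n = 18: 10.1 points, upper limit 95 + 10.1 = 105.1%
- n = 19: 9.8 points, upper limit 104.8%

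True coverage at p = 0.95 is 60% (n = 18) and 62% (n = 19). The main reason is that all cases are detected with probability 0.95^18 = 0.397 or 0.95^19 = 0.377. The Wald interval then collapses to the single point 100% and misses 95%.

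**3. Valid intervals at the same case counts.** The exact (Clopper–Pearson) lower limit L solves P(X ≥ x | n, L) = 0.025, and the upper limit U solves P(X ≤ x | n, U) = 0.025. The Wilson limits are [p̂ + z²/2n ± z√(p̂(1 − p̂)/n + z²/4n²)] / (1 + z²/n). For 18/19 the Wilson lower limit is (0.9474 + 0.1011 − 0.1425) / 1.2022 = 0.754.

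| Detected | Estimate | Exact 95% CI | Wilson 95% CI | Estimate minus lower limit, exact / Wilson | Half-width, exact / Wilson |
|---|---|---|---|---|---|
| 17/18 | 94.4% | 72.7–99.9% | 74.2–99.0% | 21.7 / 20.2 | 13.6 / 12.4 |
| 18/19 | 94.7% | 74.0–99.9% | 75.4–99.1% | 20.8 / 19.4 | 12.9 / 11.9 |
| 21/22 | 95.5% | 77.2–99.9% | 78.2–99.2% | 18.3 / 17.3 | 11.4 / 10.5 |
| 18/18 | 100% | 81.5–100% | 82.4–100% | 18.5 / 17.6 | 9.3 / 8.8 |
| 19/19 | 100% | 82.4–100% | 83.2–100% | 17.6 / 16.8 | 8.8 / 8.4 |

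The 22 cases are 200 × 0.11, that is, no losses at all. Averaged over the binomial distribution at p = 0.95, the distance from the estimate to the exact lower limit is 21, 20 and 18 points for 18, 19 and 22 cases.

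**4. What a 10-point margin would take.** An exact lower limit within 10 points needs about 50 cases if the expected distance is the criterion, or about 52 if the estimate is fixed at 95% (52 / 0.11 = 473 patients). If only the half-width must be 10 points, about 29 cases are needed with exact limits (29 / 0.11 = 264 patients) or about 25 with Wilson (227 patients).

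**5. Specificity.** 141/148 = 95.3%, exact 90.5–98.1%: 4.8 points below, 2.8 above, half-width 3.8.

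**6. Target condition, side by side.** Section 4.1 sizes on residual disease or recurrence. Sections 3.4 and 6.3 compute sensitivity in patients who develop recurrence and specificity in those who stay free of it. Section 1.1 speaks of residual disease and of recurrence as separate findings. No split of the 18–19 is given. As an assumption only: if 0 to 3 of 19 were residual disease and were left out, the exact lower limit with one missed case would run from 74.0% (18/19) to 69.8% (15/16).

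**The case against.** Several objections have force.

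- **The 167 is correct on its own terms.** Section 4.1 cites a published calculator method and gives every input, and the figure reproduces. A reader might infer a calculation slip. There is none: the weakness is the approximation and the precision claimed from it.
- **A margin of error is conventionally a half-width**, not a promise about the lower limit. On that reading the shortfall for the planned result at 18–19 cases is only about 2–4 points (11.9–13.6 against 10). If every case is detected, the half-width is below 10, and with 22 cases Wilson comes close (10.5). This limits the size of the point but does not remove it. The planned result still misses the margin, the 22 cases require that nobody is lost although the increase to 200 is reserved for losses, and the interval is so lopsided that a symmetric margin misdescribes it.
- **Nothing commits the analysis to a Wald interval.** A reader might infer that the published interval will have 60% coverage. Section 6.3 names no method, and that choice may properly sit in an analysis plan that is not shown. The low coverage describes only the planning approximation.
- **No sentence excludes residual disease from the endpoint.** A reader might infer that the endpoint leaves such patients out and that case numbers will therefore fall. The article uses recurrence loosely: Section 9 passes from residual disease or recurrence to detection of recurrence. The 11% also fits the 10–15% that Section 1.1 gives for recurrence. The mismatch is one of wording to reconcile, and not evidence of fewer cases.
- **No threshold or decision rule depends on the margin**, and the published intervals will show the real uncertainty. That argues for a lower severity, not for leaving the statement as it is.

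**Conclusion.** The point holds as a statement of precision that the plan's own case count does not support. At 95% sensitivity and 18–19 cases, valid 95% intervals place the lower limit about 19–22 points below the estimate, with a half-width of about 12–14 points. With all 200 patients evaluable the exact lower limit is still 18.3 points below (21/22). Precision for specificity is adequate. This assumes the plan's 11% prevalence and 95% sensitivity, and one binomial outcome per patient.

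The mismatch in target condition is a separate and smaller matter. Its effect on case numbers cannot be sized from the document, and the precision point does not depend on it.

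Both should be fixed. Neither calls for a larger study, and neither invalidates the design.

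**What to change.** 1. **Section 4.1:** keep 200 patients. Replace the 10% margin for sensitivity with the interval the design is expected to give, naming the method behind it. For example: with 18–22 cases and one missed, the exact or Wilson 95% interval has a lower limit of about 73–78% and an upper limit of about 99–100%. State that specificity is precise to about ±4–5 points.
2. **Sections 3.4, 4.1 and 6.3:** use one target condition. Either state that verified residual or recurrent disease after primary treatment counts as disease-positive, with recurrence only as a secondary analysis, or keep recurrence only and adjust the expected number of cases in Section 4.1.

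The cost is wording in three sections and a less favourable precision statement. No patients, samples or visits are added. The changes are best made before the one-year interim results that Section 7.1 intends to publish.

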### 4.2. Recruitment

After the diagnosis of OPSCC, eligible patients are screened for eligibility before written informed consent is obtained. A recruitment letter and written participant information are sent digitally via the Danish Digital Post, inviting the patient to participate in the study. The written participant information, as well as the pamphlets “Forsøgspersoners rettigheder i et sundhedsvidenskabeligt forskningsprojekt” (“Rights of test subjects in a health scientific research project”) [15], and “Før du beslutter dig” (“Before deciding”) [16], is sent before the patient attends the first treatment consultation at the Department of Otolaryngology, Head and Neck Surgery and Audiology, Copenhagen University Hospital—Rigshospitalet. After the written participant information has been sent, a member of the research group will contact the potential participant by phone and arrange an oral presentation of the study before or after the first treatment consultation. If the potential participant does not answer the phone or respond to the invitation before the consultation, the treating physician may invite the patient to participate in the study and ask whether the patient is interested in an oral presentation of the project. If the patient wishes to participate, written informed consent is obtained.

## 5. Methods: Assignment of Interventions

### 5.1. Randomization

This study is non-randomized. All included patients will follow the same follow-up program, with blood samples collected at the same intervals as the standard clinical follow-up program for a minimum of two years and up to three years.

### 5.2. Blinding

No blinding is performed. Results of each ctHPV-DNA analysis will be communicated to the treating physician, the patient, and the study investigators.

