### 1.2. Objectives

The aim of this study is to investigate whether prospective and systematic ctHPV-DNA testing can improve the standard follow-up program for patients with HPV+ OPSCC by detecting recurrence earlier than, or simultaneously with, conventional clinical or radiological assessment.

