### 3.5. Harms

In general, blood sampling is considered a minimally invasive and simple procedure. When blood is drawn, transient pain at the venepuncture site and minor bruising may occur. This will pass within a few days. Patients participating in this study are covered by the Danish Patient Compensation Association (Patienterstatningen) in the event of study-related injury. The information leaflets “Forsøgspersoners rettigheder i sundhedsvidenskabelige forskningsprojekter” and “Før du beslutter dig” will be included with the written participant information [15,16]. Participants experiencing any adverse events that may be related to the study will be instructed to contact the study investigators.

Every patient with a positive ctHPV-DNA sample after completion of treatment will be referred for a PET/CT scan to assess whether there is evidence of clinical recurrence. The scan is a standard diagnostic PET/CT (2-(flourine-18) fluoro-2-deoxy-D-glukose (FDG)-PET/CT). During the PET part of the scan, the radioactive sugar FDG will be injected. PET has no known side effects. The CT part of the scan is performed using intravenous iodinated contrast medium. Immediately after injection, some patients may experience a transient sensation of warmth, a metallic taste, or an urge to urinate. As with any medicinal product, iodinated contrast medium carries a risk of allergic reactions upon injection. Approx. 5% of patients will experience minor side effects, including transient nausea, itching or rashes, whereas the risk of serious adverse reactions is very low (<0.1%). If the patient has previously experienced a severe reaction to IV contrast medium, the PET/CT can be conducted without the use of IV contrast medium. Some patients may experience claustrophobia during the scan, but trained staff will always be present to provide assistance if needed. Some participants may also undergo repeated PET/CT scans due to positive ctHPV-DNA blood samples and no evidence of recurrence, resulting in additional exposure to ionizing radiation. The associated risk is considered low, and only a small number of patients are expected to undergo more than one additional PET/CT scan.

Finally, patients with positive ctHPV-DNA blood samples but without evidence of recurrence may experience increased anxiety. However, this is expected to affect only a small number of patients, which is one of the reasons why the Fear of Cancer Recurrence Questionnaire has been included in the study.

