The blood samples are collected in Streck Cell-Free DNA BCT CE tubes. These tubes are designed to stabilize blood cells and prevent the release of genomic DNA for up to 7 days at room temperature, thereby minimizing contamination of cell-free DNA and enabling the extraction of high-quality cell-free DNA. Samples will be stored at room temperature for up to four days before processing. Approx. 8 mL plasma/patient (corresponding to two Streck Cell-Free DNA BCT CE tubes) will be isolated by centrifugation at 2250× *g* for 10 min. The isolated plasma will subsequently be centrifuged at 16,800× *g* for 10 min to remove any residual cells or cellular debris before storage at −80 °C. DNA will be extracted using the QIAamp Circulating Nucleic Acid Kit (#55114) on a QIACube instrument and eluted in 60 µL. DNA concentration and purity will be assessed using NanoDrop (Thermo Fischer Scientific, Waltham, MA, USA) or TapeStation (Agilent Technologies, Santa Clara, CA, USA). The following quality control (QC) assays will be used: QC assay 1. DNA purification efficiency will be assessed at the batch level by analyzing five healthy donor plasma samples spiked with the 191-bp CPP1 DNA spike-in before and after each batch of patient samples, instead of adding CPP1 DNA directly to the individual patient samples, allowing estimation of the mean DNA loss during extraction [20]. Batch-level controls were chosen instead of sample-level spike-in controls to avoid introducing exogenous DNA into individual clinical samples while preserving native patient DNA for future analyses. QC assay 2. Genomic DNA contamination (white blood cell contamination) will be assessed in native patient DNA as previously described [12] or using TapeStation. QC assay 3. Sample fragmentation will be assessed in native patient samples as previously described. All QC assays adhere to the guidelines published by the Danish ctDNA Research Center [12,21]. The amount of HPV-DNA in plasma and the specific HPV genotype will be assessed by our ultrasensitive droplet digital PCR (ddPCR) assay, which we have developed to assess eight high-risk HPV genotypes: HPV16, 18, 31, 33, 35, 45, 51, and 58 [12,15,16]. First, each sample will undergo a 12-cycle PCR pre-amplification containing only one HPV primer set together with the EMC7-65 primer set. Second, ddPCR analysis will be performed using the same HPV and EMC7-65 primer set (final concentration 900 nM) together with the corresponding probes (final concentration 250 nM). A sample is considered ctHPV-DNA positive when at least five HPV+ droplets are detected for the relevant HPV genotype. Samples with 5–20 HPV+ droplets, corresponding to results close to the analytical detection limit, will be confirmed using a second blood sample to minimize false-positive and false-negative results. If the second blood sample confirms HPV-DNA positivity, the sample is classified as positive. If the second blood sample is negative, the result is considered discordant, and the first blood sample is re-analyzed. The analytical limit of detection (LOD) has been internally defined as the lowest HPV-DNA concentration corresponding to five HPV+ droplets in the ddPCR analysis, corresponding to 1.9 double-stranded HPV-DNA copies/mL plasma. No formal limit of quantification (LOQ) has been established, as the assay was developed for sensitive detection rather than precise quantification at very low copy numbers. ddPCR runs were considered invalid in cases of failed droplet generation, insufficient accepted droplet count, positive droplets in the negative control, failed positive controls, or insufficient EMC7 amplification, indicating an inadequate sample quality. Samples with evidence of excessive genomic DNA contamination or poor cfDNA fragmentation quality were repeated or excluded from further analysis. The ddPCR assay is conducted at MDxCore, Department of Clinical Biochemistry, Copenhagen University Hospital—Rigshospitalet.

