### 6.3. Statistical Methods

The primary outcome, namely the sensitivity and specificity of ctHPV-DNA for detecting recurrence, will be calculated with 95% confidence intervals. Sensitivity will be determined among patients who develop recurrence, and specificity among patients who remain recurrence-free during follow-up. Positive predictive value will be determined among patients with positive ctHPV-DNA samples, and negative predictive value among patients with negative ctHPV-DNA results.

Only recurrence confirmed by a clinical and/or radiological examination will be regarded as recurrence. Histopathological confirmation will be included in the clinical verification if tissue sampling is feasible during the clinical examination.

The primary analyses will include all enrolled patients with a ctHPV-DNA baseline blood sample and at least one post-treatment blood sample, and follow-up assessment. Patients will be analyzed according to their clinical follow-up data, irrespective of the completeness of subsequent blood sampling or imaging, to minimize bias and reflect a real-world clinical practice.

Time-to-event outcomes, including time to recurrence detected by ctHPV-DNA and time to recurrence detected by clinical and/or radiological examination, will be analyzed using Kaplan–Meier survival curves. Median time to recurrence and corresponding 95% confidence intervals will be reported. Comparisons between ctHPV-DNA detection and standard surveillance will be performed using the log-rank test.

Healthcare utilization endpoints, including the number of PET/CT scans and Cancer Fast-Track referrals without evidence of recurrence, will be summarized using descriptive statistics (mean, median, standard deviation, and interquartile range). Between-group comparisons (e.g., patients with versus without recurrence) will be performed using *t*-tests for normally distributed variables or Mann–Whitney U tests for non-parametric distributions.

Analyses will use all available data, and, where appropriate, missing data will be handled using multiple imputation under the assumption that data are missing at random (MAR).

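### Every ctHPV-DNA result is released and positives trigger the work-up, yet nothing secures a record of what standard follow-up found without the result, so test-led and clinician-led detection cannot be reliably separated

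*Protocol article*

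**What the plan says.** **Release of results.** Section 5.2 of the protocol article states "No blinding is performed" and continues: "Results of each ctHPV-DNA analysis will be communicated to the treating physician, the patient, and the study investigators".

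**Aim.** Section 1.2 asks whether testing improves follow-up by "detecting recurrence earlier than, or simultaneously with, conventional clinical or radiological assessment". Section 3.4 makes the time to recurrence by each route a secondary endpoint, and section 6.3 compares the test with standard surveillance by a log-rank test.

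**Reference standard.** Accuracy is judged "using clinically or radiologically verified recurrence as the reference standard" (3.4). Section 6.3 adds: "Only recurrence confirmed by a clinical and/or radiological examination will be regarded as recurrence". Tissue is conditional: "Histopathological confirmation will be included in the clinical verification if tissue sampling is feasible during the clinical examination".

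**Consequence of a positive test.** "Every patient with a positive ctHPV-DNA sample after completion of treatment will be referred for a PET/CT scan" (3.5). Sections 3.3 and 4 place a clinical examination before the scan. Section 4 adds a repeat sample three months later if nothing is found, and a second work-up if that sample is positive.

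**Timing and records.** Blood is drawn on the schedule of the standard visits (4, 5.1). On handling, section 6.1 says: "Samples will be stored at room temperature for up to four days before processing". The clinical items that section 6.1 takes from medical records include recurrence status, imaging findings and status at the last examination. It lists no verdict for each visit dated against release of the result.

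**The concern.** The aim compares two detection routes, so it needs to be known what each would have found without the other. Under this plan the conventional route is not observed alone. Once a sample is positive, the clinician knows it, and the examination and scan that follow take place because of it. The date then recorded as clinical or radiological detection is partly a product of the test.

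Two different situations therefore look alike in the data. In one, the clinician already suspected recurrence at the visit where the positive sample was drawn. In the other, nothing was suspected and the test alone raised the alarm. Only the second supports a claim of earlier detection. If the distinction is reconstructed afterwards from notes, by people who know the result, the label is open to influence.

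The reference verdict is exposed too. It can rest on judgement without histology, it is reached with the result known, and test-negative patients receive no scan triggered by the study.

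**Working it through.** **1. Where knowledge of the result can enter**

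| Step | Result known? | Source |
|---|---|---|
| Verdict given at the scheduled visit, same-day sample | Normally not yet; turnaround is not stated | 4, 5.1, 6.1 |
| Same visit, results of earlier samples | Yes | 5.2 |
| Examination and PET/CT after a positive sample | Yes, by design | 3.3, 3.5, 4 |
| Scan reading and confirmation of recurrence | No masking stated; 5.2 says there is none | 5.2, 6.3 |
| Test-negative patients | Known negative, no study-triggered scan | 3.3, 3.5, 5.2 |

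The first row is the one point where an opinion uninfluenced by the current sample normally exists. The article does not say that it is captured before release.

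**2. The plan's own sample size** (section 4.1: sensitivity 95%, margin 10 points, two-sided 5%, prevalence 11%)

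- Cases needed: 1.96² × 0.95 × 0.05 / 0.10² = 18.25.
- Total: 18.25 / 0.11 = 165.9, rounded up to 166. The plan states 167, which agrees within rounding.
- Split: 167 × 0.11 = 18.4 with disease and 167 × 0.89 = 148.6 without, matching the stated 18–19 and 148–149.

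The fix below does not change these figures.

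**3. Weight of one case**

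- 1/19 = 5.3 points and 1/18 = 5.6 points, just over half of the 10-point margin.
- 18/19 = 94.7% (exact 95% CI 74.0 to 99.9%). 17/19 = 89.5% (66.9 to 98.7%).

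This is how much any single case counts among so few. It does not say how many cases would be relabelled.

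**4. Direction of bias in sensitivity and specificity (illustration)**

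The documents give no influence rates, so those used here are assumptions. Let *f* be the share of false positives called recurrence because the result was known, and *g* the share of test-negative recurrences not called for the same reason. Take N = 167, prevalence 11% and true specificity 95%.

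At true sensitivity 95%: true positives 0.95 × 18.37 = 17.45, false negatives 0.92, false positives 0.05 × 148.63 = 7.43, true negatives 141.20. PPV = 17.45 / 24.88 = 70%.

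Apparent sensitivity = (TP + *f*·FP) / (TP + *f*·FP + (1 − *g*)·FN). Apparent specificity = (TN + *g*·FN) / (TN + *g*·FN + (1 − *f*)·FP).

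| True sensitivity | *f* = 10%, *g* = 25% | *f* = 25%, *g* = 50% |
|---|---|---|
| 95% | 96.4% | 97.7% |
| 85% | 88.8% | 92.7% |
| 75% | 80.8% | 87.2% |

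Apparent specificity is about 95.5% in the first scenario and 96.2–96.3% in the second. At true sensitivity 95%, PPV rises from 70% to 73% and 78%. Every scenario favours the test.

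**The case against.** **Open release is deliberate.** The abstract and Discussion present clinical action on positive results as a feature of the study. Withholding results from clinicians would defeat it. This stands: the absence of blinding is not in itself the fault. A record made before release does not conflict with it.

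**Order of data entry is operational detail.** A condensed article may leave it to the full protocol, which is not shown. This has some force, and if such a rule exists there, citing it would largely settle the point. But section 5.2 is not silent: it rules out blinding and states no limit for the verdict that defines recurrence.

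**A stronger reading is not supported.** A reader might infer that the verdict at a visit is shaped by that same visit's result. The documents do not show this. The assay follows the blood draw and needs centrifugation, extraction, pre-amplification and ddPCR, with a second blood sample for 5–20 positive droplets. A verdict given at the visit would normally come first. The four days are a maximum storage time, however, so the order is likely rather than guaranteed.

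**A locked entry does not cure the main exposure.** A reader might also infer that locking would protect the whole comparison at no cost. It would not: triggered work-up, scan reading with the result known, unequal imaging and knowledge of earlier results all remain. Nor do the documents support a claim of zero staff cost.

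**Suspicion is not the endpoint.** Sections 3.4 and 6.3 count verified recurrence only. A visit-day suspicion used as the conventional result would change the endpoint and would miss recurrences that present between visits. This stands and shapes the fix: the entry must supplement verified recurrence, not replace it.

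**Conclusion.** The point holds in a limited form. The plan secures no record of what standard follow-up found without the result, so the question in section 1.2 and the time-to-detection comparison in section 6.3 cannot be answered cleanly. The change is worth making because it is small and leaves the planned handling of results as it is.

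The size of the bias is unknown. One relabelled recurrence is worth 5.3–5.6 points among 18–19 cases, and the scenarios above show direction only, under assumed rates. No corrected sensitivity or specificity can be derived. The conclusion assumes that no lock before release is laid down in a document not shown, and that a visit verdict normally precedes the result.

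**What to change.** 1. At each scheduled visit, record in REDCap whether recurrence is suspected and on what basis. Time-stamp the entry and lock it before that sample's result is released. Results then go out as planned.
2. Keep clinically or radiologically verified recurrence as the reference standard for sensitivity and specificity.
3. Use the locked entry only to classify verified recurrences: suspected by the clinician at that visit (simultaneous), or first raised by the test (earlier). Classify recurrences that arise between visits by what prompted the work-up.
4. State as a limitation that this protection is partial. It does not remove bias in sensitivity and specificity from result-triggered work-up, from scans read with the result known, from unequal imaging of test-negative patients, or from knowledge of earlier results.

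The cost is one extra field per visit, with no additional visits and no change to the sample size. That the staff burden is low is an assumption; the documents give no figure.
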